## Hypotheses

2

The main goal of the presented RCT protocol is to evaluate how 8 weeks of neurofeedback mindfulness using a wearable EEG headband could moderate headache experience (including frequency and intensity), headache management self-efficacy, psychiatric symptoms (i.e., anxiety and depression) and dependence on analgesics for adults with chronic migraine who are also identified as naïve meditators. The specific measures are described in more detail below. The following hypotheses are tested in this RCT.1.After completing the intervention, neurofeedback mindfulness will improve headache experience across time via:a.Decreased migraine disabilityb.Decreased migraine intensityc.Increased headache management self-efficacya.Decreased anxietyb.Decreased depressionc.Decreased level of dependence on medication.2.Participants in the neurofeedback mindfulness group will have significantly lower scores in migraine disability and intensity, and significantly higher scores in headache management self-efficacy when compared to the attention control group and the waitlisted group.3.Participants in the neurofeedback mindfulness group will have lower anxiety and lower depression scores when compared to the attention control group and the waitlisted group.4.Neurofeedback mindfulness participants will have a significant decrease in the level of dependence on medication, compared to those in the controlled intervention and waitlisted groups.5.There will be no impact of participants' belief in meditation on any of the measured criteria (e.g., migraine characteristics and psychiatric symptoms) across time.

## Methods

3

### RCT design

3.1

This protocol proposes a longitudinal RCT to compare neurofeedback mindfulness with two control groups: a simple attention intervention and a waitlisted group. Similar to the previous RCTs in mindfulness and migraine, the duration of this trial is scheduled for 8 weeks [20,[34], [35], [36]] with a 10-min practice per day [17]. This study protocol includes two major phases: Phase I for RCT design preparation and Phase II for data collection.

During Phase I, plans are made for participant recruitment and ensuring that all ethical concerns are met. Since the portable EEG is connected to the third-party app (also named MUSE) on smartphone, plans should be made to ensure that no personal identifiable details are shared on the app. Importantly, the researchers are required to monitor the participants' activities on the MUSE app every day. Due to these factors, we will equip all the participants with generic coded emails that are de-identified for completing the surveys on SurveyMonkey and registration of participants on the MUSE app. The generic emails are all connected to our lab's email so that the researchers can verify and proceed with MUSE app's registration process for each participant. Prior to data collection, it is necessary to sign up for a platform, called MUSE Connect, which provides a list of all the participants' practices for daily monitoring of the groups' exercises. The university-based generic emails are available throughout all the study and their codes will be used to refer to the participants. Phase II of this study includes posting announcements seeking adults with chronic migraine in neurology clinics, contacting volunteers, accepting participants, scheduling device delivery, initial device and app set up, data collection monitoring, and daily reminders for the tasks to the participants.

### Study procedure

3.2

Participant recruitment occurs through neurology clinics and walk-in clinics in Saskatoon, Canada. The posters will be emailed to individuals who have been referred to the clinics. Once the volunteers email the lab, the initial questionnaire and consent forms will be shared with them. The initial questionnaire includes 45 open-ended and multiple-choice questions (estimated to take 26 min to complete on average) about descriptive information, migraine characteristics and history of the participants as well as their background experience with meditation and whether they believe that meditation could help their migraine headaches. The participants’ history of taking analgesics and acute medications will be assessed based on severity of dependence scale (SDS) [37].

### Eligibility screening

3.3

All the participants will be screened for eligibility before an invitation is sent to them. To be eligible, the participants should 1. be over 18 years of age, 2. have a diagnosis of chronic migraine from a clinician or have met the criteria for a chronic migraine diagnosis based on ICHD-3 [5], 3. have no frequent background experience of meditation, 4. reside in Saskatoon or be able to receive the device from Saskatoon and the communities nearby, 5. have a smartphone and internet connection for accessing the MUSE app. The exclusion criteria for this study consist of.1.Comorbidity of Raynaud's syndrome or diabetes,2.Plans to start a new preventative migraine treatment.

After checking eligibility criteria, the participants will be randomly allocated in the three arms of the study: the neurofeedback mindfulness, the controlled intervention, and the waitlisted group. The participants will receive an invitation letter with a description of their task, the PDF form of their consent, and the contact information of the researcher in charge of the device delivery.

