### The assigned tasks

3.6

In this study, the participants will be randomly allocated in three groups of neurofeedback-mindfulness, the controlled intervention, and waitlisted groups. The allocation will be done using stratified randomization to ensure equal distribution (1:1:1) among groups.1.The neurofeedback mindfulness groupThis group is asked to sit comfortably in a quiet area and do one of ten beginner self-guided mindfulness sessions on mind-body scanning techniques from within the MUSE app. Each session includes a brief explanation for 2–3 min before the practice. The participants repeat the same sessions throughout the intervention.1.Introduction to mindfulness: a brief review of mindfulness as a nonjudgmental observation of body and mind.2.Training a puppy: how to monitor emotions and control reactions to different states of mind.3.Sensation of breath: the importance of mindful breathing techniques.4.Counting breaths: how to inhale and exhale properly.5.Sitting comfortably: how to modify positions for mindfulness practices.6.Finding your soundscapes: monitoring the states of mind and how they are associated with the given neurofeedback sounds.7.Dealing with distraction: describing nonreactivity and acceptance of different states of mind.8.Working with discomfort: how to mindfully adjust the states of mind in unfavourable conditions.9.Lowering the bar: Moderating expectations from practices and accept the present state of mind without changing it.10.Bridging to daily life: bringing attention to how the state of acceptance could be conceptualized in everyday routines.

Once the participants start their practices, they receive sounds for their real-time brain activities: thunderstorm for an active state, ocean waves for a neutral state, and birds chirping for a relaxed state. For each 5 s of consistent relaxed state, the participants are reinforced with points.2.The attention control group

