### Blinding

3.8

Due to the nature of this RCT design, it is not possible for participants to be blinded to their group assignment. However, the subjects in all three groups will be coded and de-identified after initial meeting for the whole duration of data collection and data analysis procedure. They are requested to keep their contact by mentioning their given codes and fill out the questionnaires by submitting the USASK coded emails instead of their personal emails.

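### The exclusion on preventives looks only forward, so recent starters can enrol and their improvement is counted in the within-arm change over time (hypothesis 1), though not, in expectation, in the randomised comparison

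*Protocol article*

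**What the plan says.** Section 3.3 (Eligibility screening) gives two exclusions. One concerns comorbid conditions. The other is "Plans to start a new preventative migraine treatment". The article states no period of stable preventive use, no exclusion for a recent start or change, and no rule for an unplanned start during follow-up.

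Section 3.2 (Study procedure) describes the source population: "Participant recruitment occurs through neurology clinics and walk-in clinics in Saskatoon, Canada", and "The posters will be emailed to individuals who have been referred to the clinics". The initial questionnaire there has 45 questions, including migraine history. The medication history it names covers analgesics and acute drugs, scored with the SDS; preventives are not named.

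Section 2 words hypothesis 1 as change over time: "After completing the intervention, neurofeedback mindfulness will improve headache experience across time". Hypotheses 2-4 compare the meditation arm with the attention control and the waitlist. Section 3.12 (Statistical methods) says the study rests mainly on comparing baseline with Weeks 4 and 8 by repeated measures ANOVA, and adds the time-by-group interaction for each scale.

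On design, section 3.6 states: "The allocation will be done using stratified randomization to ensure equal distribution (1:1:1) among groups". Section 3.1 says "the duration of this trial is scheduled for 8 weeks", and section 3.8 says "it is not possible for participants to be blinded to their group assignment".

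**The concern.** An exclusion for a planned new preventive has one plausible purpose: to stop another treatment's early effect from appearing in the 8-week outcomes. A preventive begun the week before Week 1 threatens those outcomes in the same way as one planned for the week after, yet only the second is excluded. Among people referred to neurology and walk-in clinics, recent changes of treatment are plausible, though the article gives no figure.

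At stake is the reading of change over time. If some of the meditation arm are still improving on a recently started preventive, that improvement is part of the change that hypothesis 1 credits to neurofeedback mindfulness. The main effect of time, pooled over the three arms, is affected in the same way. Randomisation does not protect either result, because neither is a comparison between arms.

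A second, weaker route concerns people with no plan at screening who start a preventive during the 8 weeks. Participants know their arm, so such starts could differ between arms.

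**Working it through.** The plan gives no figure on this point, so there is none to reproduce. The share of starters and the size of a preventive's effect below are assumptions, shown as ranges.

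**Inputs**
- From sections 3.9 and 3.10: 180 allocated and 50% attrition, so 180 × (1 − 0.50) = 90 completers, or 30 per arm if losses are equal. The article expects more loss in the two task arms, so equal losses are a simplification.
- Assumed: share of an arm with a recently started preventive, q = 10-30%.
- Assumed: improvement from that preventive over 8 weeks, e = 0.3-0.8 SD of the change score, added to any intervention effect.

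**1. Spurious within-arm change**

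Expected spurious change = q × e.
- Low end: 0.10 × 0.3 = 0.03 SD.
- Middle: 0.20 × 0.5 = 0.10 SD.
- High end: 0.30 × 0.8 = 0.24 SD.

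With 30 completers, the standard error of an arm's mean change is 1/√30 = 0.18 SD. The spurious change is therefore between a small fraction of one standard error and about 1.3 standard errors (0.24/0.18).

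**2. Effect on the tests**

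This was simulated with no intervention effect, 30 completers per arm, 20,000 runs, a nominal two-sided 5% level for the tests of change over time, and loss to follow-up unrelated to recent starts. Rejection rates:

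| Assumption | Change in one arm | Change pooled over 90 | Difference between arms |
|---|---|---|---|
| q = 20%, e = 0.5 | 8% | 15% | 4.9% |
| q = 30%, e = 0.8 | 22% | 56% | 5.2% |

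The tests of change over time lose their nominal level. The between-arm test keeps it.

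**3. What is left in the between-arm comparison**

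Starts before randomisation balance in expectation. The chance imbalance between two arms has SD = e × √(2q(1 − q)/n), with n = 30:
- q = 10%, e = 0.3: 0.3 × √(0.18/30) = 0.02 SD.
- q = 30%, e = 0.8: 0.8 × √(0.42/30) = 0.09 SD.

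This is added variance, not bias.

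**4. Unplanned starts during the 8 weeks**

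Bias in the contrast = e × (difference between arms in the share who start). If 5% start in one arm and 15-25% in another (assumed):
- Low end: 0.3 × (0.15 − 0.05) = 0.03 SD.
- High end: 0.8 × (0.25 − 0.05) = 0.16 SD.

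If the higher share is in the waitlist, the contrast understates a benefit of meditation. With equal shares, the bias is zero.

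**The case against.** **Randomisation handles recent starters.** Hypotheses 2-4 and the interaction compare three concurrent arms allocated 1:1:1. This stands. A reader might infer that the preventive's effect would be taken for the intervention's in those comparisons too. The design does not support that, and the between-arm rejection rates of 4.9% and 5.2% agree.

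**The cases may be identifiable after all.** A reader might infer that preventive starts could never be traced, since none of the six repeated scales is described as recording them. That goes too far. The initial questionnaire covers migraine history, and section 3.12 says the diaries will be used to follow headache medication. Their items are not shown, so whether preventives and start dates are captured is unknown. Sections 3.5 and 3.6 describe the diaries only for the waitlist.

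**An article condenses the full protocol.** Further rules on other treatments may exist there, so their absence is not counted as a fault here. The point concerns a criterion that the article does state and that, as worded, covers only half of its evident purpose.

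**Differential starting is speculation.** The article offers no evidence that waitlisted participants would start more preventives, and anyone already planning to start is excluded. This stands: it is a possibility in an unblinded trial, not an expected bias.

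**An eligibility line does not rescue an uncontrolled change.** Regression to the mean, natural course and expectancy also enter hypothesis 1. This stands too, and is why the fix includes resting the conclusion on the contrast between arms.

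**Conclusion.** The concern holds for change over time. The exclusion leaves out people who have recently started or changed a preventive, and their improvement is confounded with the intervention's in hypothesis 1 and in the main effect of time. If 10-30% of an arm are such starters with an effect of 0.3-0.8 SD, the spurious change is 0.03-0.24 SD. Both ranges are assumptions, so this illustrates the size of the problem and does not estimate it.

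It does not hold as a claim of bias in the randomised comparison. Recent starts add variance there, with a chance imbalance of about 0.02-0.09 SD at 30 completers per arm. That contrast is biased only if unplanned starts during the 8 weeks differ by arm, by 0.03-0.16 SD on the shares assumed. Balance in expectation also presumes that loss to follow-up is unrelated to recent starts.

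The gap is worth closing before recruitment, because start dates are hard to recover reliably afterwards.

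**What to change.** 1. Extend the existing exclusion to preventives started or changed within a stated period before Week 1, checked in the initial questionnaire. One trial length (8 weeks) is an example; the sponsor should choose and justify the window.
2. At Weeks 4 and 8, ask all three arms whether a preventive has been started or changed since the last form, and when, unless the diaries already record this in every arm. Report the counts by arm.
3. Keep all participants in the main analysis, and rest the efficacy conclusion, including that of hypothesis 1, on the time-by-group contrast. Present within-arm change as description.
4. If an analysis sets aside data after a preventive start, label it a sensitivity analysis and state its risk: it conditions on an event after randomisation that may differ by arm, so it can introduce selection bias.

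The cost is one eligibility line, one questionnaire item and one short table. The downside is that some volunteers are deferred until the window has passed. Nothing here changes participants' care.

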### Initial meeting

3.4

For the two intervention groups, an online meeting will be scheduled (estimated 30–60 min) after the participants receive the device. During the session, the following steps will be checked.•A brief introduction to the study goals and tasks•Request for a verbal consent to proceed with the meeting•Help with setting up and wearing the headband•Downloading and signing into the MUSE app•Tutorials on the assigned practice, and device calibration

The participants are required to complete the pre-intervention questionnaire on the day of the initial meeting.

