### Participants

3.9

According to A priori G*power software calculation for this study considering both between-subject and within-subject effects, a sample size of 66 is expected to detect significance level of 0.05 with 95 % power through our planned statistical analysis test, i.e., Repeated Measures ANOVA. We aim to look at the effect of time by comparing the baseline with mid-/post intervention reports of the participants for each of the six measurements independently; moreover, we will compare the interaction of time*groups separately for each of our six scales. We will initially allocate 180 participants; yet with reference to the previous studies [22], we could expect up to 50 % of attrition. After applying inclusion and exclusion criteria, participants will be selected for either the meditation, the control, or the waitlisted group. We speculate a higher number of attritions in the meditation and control groups regarding the complexity of the given tasks as compared to the waitlisted group. Fig. 3 provides a flowchart for the number of expected participants at each stage of the study.

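### The arm is disclosed in the invitation letter before the Week 1 scales are completed, and possibly before consent is signed, so entry into the analysed groups can depend on the arm

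*Protocol article*

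**What the plan says.** The protocol article gives the order of steps across several sections.

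- **3.2 Study procedure.** "Once the volunteers email the lab, the initial questionnaire and consent forms will be shared with them". The initial questionnaire asks about migraine characteristics, meditation experience and "whether they believe that meditation could help their migraine headaches". At this stage the "history of taking analgesics and acute medications will be assessed based on severity of dependence scale (SDS").
- **3.3 Eligibility screening.** "All the participants will be screened for eligibility before an invitation is sent to them". Next, "After checking eligibility criteria, the participants will be randomly allocated in the three arms of the study". The sentence after that describes the letter: "The participants will receive an invitation letter with a description of their task, the PDF form of their consent".
- **3.4 Initial meeting.** The two task arms receive the device, attend an online meeting of 30–60 minutes and complete the pre-intervention questionnaire on that day.
- **3.5 and 3.6.** The waitlist is told its assignment and completes Week 1 after being invited. It receives the device only once all three rounds of questionnaires are done.
- **3.7 Incentives.** Participants keep the headband, including those who withdraw before completion.
- **3.8 Blinding.** Participants are not blinded.
- **3.9 Participants.** "We will initially allocate 180 participants", with up to 50% attrition expected, and more of it in the two task arms than in the waitlist.

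**The concern.** Randomisation makes the three groups comparable as allocated. The planned repeated measures ANOVA (3.12) uses people with scores, and all Week 1 scores come after the participant has read which arm they are in. Anyone who leaves at that moment has no Week 1, 4 or 8 record.

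The reasons for leaving can differ by arm. A sceptic may not want to meditate daily, a hopeful volunteer may not want to browse email for 10 minutes, and another may not want to wait 8 weeks. The steps and incentives before Week 1 differ too. Belief in treatment is a plausible driver, and the Introduction itself links belief to reported improvement in headache sufferers. If belief affects both who stays and how they change, the time-by-group comparison in hypotheses 2 to 4 no longer compares like with like. The analysis of belief under hypothesis 5 is affected as well.

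This is separate from the effect of knowing the arm on the answers of those who stay.

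**Working it through.** **Step 1: order of events.** Putting the sections side by side gives: first contact with questionnaire and consent forms (3.2); eligibility check (3.3); random allocation (3.3); letter naming the person's task (3.3); then Week 1 scales, on the day of the initial meeting in the task arms (3.4) and after the invitation in the waitlist (3.5). Disclosure precedes Week 1 in all three arms. The text does not say when consent is signed.

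**Step 2: what exists for someone who leaves at disclosure.** Available: SDS-based medication history, belief in meditation, migraine characteristics and meditation experience (3.2). Not available: MIDAS, HIT-6, HMSE, BAI and CES-D, which section 3.11 first schedules at Week 1.

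**Step 3: possible size.** The article gives no figure for refusal before Week 1, so there is no stated number to reproduce. The inputs below are assumptions, apart from the arm size.

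- Arm size: 180 / 3 = 60 (3.6 and 3.9).
- Refusal in a task arm, r1: 10–30% (assumed).
- Refusal in the waitlist, r0: 0–5% (assumed).
- Refuser minus acceptor difference in the outcome contrast, d: 0.3–0.5 SD, taken as equal in both arms (assumed).

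People with any Week 1 score, 60 × (1 − r):
- task arm: 60 × 0.90 = 54 down to 60 × 0.70 = 42
- waitlist: 60 × 1.00 = 60 down to 60 × 0.95 = 57

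The mean among acceptors differs from the mean among all allocated by r × d, so the task-versus-waitlist contrast shifts by (r1 − r0) × d:
- smallest: (0.10 − 0.05) × 0.3 = 0.015 SD
- largest: (0.30 − 0) × 0.5 = 0.15 SD

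**Step 4: the same mechanism through belief.** Suppose half of those allocated believe in meditation and the waitlist joins regardless of belief (all rates assumed).
- If 80% of believers and 60% of non-believers take up mindfulness, believers make up 0.40 / (0.40 + 0.30) = 57% of that arm against 50% in the waitlist. If believers differ from non-believers by 0.5 SD in change, the shift is (0.571 − 0.5) × 0.5 = 0.036 SD.
- At 90% and 50% the share is 0.45 / (0.45 + 0.25) = 64%, and the shift is (0.643 − 0.5) × 0.5 = 0.071 SD.
- With equal uptake there is no difference.

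**Step 5: does the sample size help?** 180 × 0.5 = 90 remain, above the required 66 (3.9). That protects power. It does not remove selection.

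**The case against.** The strongest reply is that this may be ordinary withdrawal in an unblinded trial. Consent forms are shared before screening, and the PDF sent with the letter may be a copy of a form already signed. An article can leave the date of signature to the full protocol. This stands: a reader might infer that people enrol only after learning their arm, but the text does not establish it. Nor does the item "Request for a verbal consent to proceed with the meeting" in section 3.4 help that reading, since it is consent to a meeting and not to the trial. If consent came first, those who leave are losses after randomisation, but their Week 1 scores are still missing.

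A reader might also infer that nothing is known about people who never start. That is not so: the data collected at first contact allow never-starters to be compared with starters and could support a missing-data model. They do not replace a baseline on the other five scales.

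A third tempting reading is that the task arms must lose more people at this point. Section 3.9 expects higher attrition there because of task complexity, but the text gives no uptake before Week 1 (Fig. 3 was not available to me). The incentives point the other way: task-arm participants hold the headband from the start and keep it on withdrawal, while the waitlist must finish three rounds of questionnaires first. The direction is open.

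Finally, a stable difference in level already present at Week 1 largely cancels in a time-by-group test. This also stands. Bias in that test needs leavers who would have changed differently over the 8 weeks, so d above must be read as a difference in the outcome contrast and not in baseline level.

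**Conclusion.** The point holds in a limited form. The article fixes an order in which the arm is disclosed before Week 1 in every group, and possibly before consent is signed. Entry into the analysed groups can therefore depend on the arm; nothing in the text shows that it will. If leavers would have had a different course, the task-versus-waitlist contrasts shift by 0.015–0.15 SD under the assumed rates, with the sign unknown and the difference d taken as equal across arms. Mindfulness versus attention control is exposed in the same way if one task is refused more often, or by different kinds of people. The likely size is modest, but later analysis can repair it only in part, so the order should be changed before enrolment.

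**What to change.** In section 3.3, reorder the existing steps:

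1. Send every eligible volunteer one invitation describing all three tasks.
2. Obtain signed consent to whichever arm is drawn, and state that this comes before allocation.
3. Have all six baseline scales completed at this point. Asking only for agreement to any arm would still leave the Week 1 scales after disclosure.
4. Only then draw and disclose the allocation, and count the 180 from that draw.
5. Report losses between allocation and the start of the task by arm, and compare never-starters with starters on the pre-allocation data.

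The cost is one rewritten letter and a questionnaire of about 13 minutes (3.11) moved forward. Volunteers unwilling to accept every arm will decline earlier, so slightly more people must be approached.
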